## 8.5. Adverse Events

**Serious adverse events** in LIFE are defined to include: death, a life-threatening adverse experience, inpatient hospitalization or prolongation of existing hospitalization, a persistent or significant disability/incapacity, or a clinically significant laboratory or clinical test result. Important medical events that may not result in death, be life-threatening, or require hospitalization may be considered serious adverse experiences if they might jeopardize the participant or might require medical or surgical intervention to prevent one of the outcomes in the definition. An example of this in LIFE is an injurious fall resulting in a fracture that occurred during walking for physical activity.

For LIFE purposes, an **adverse event or experience** is defined as any health-related unfavorable or unintended medical occurrence that happens during the process of screening or after randomization. Certain adverse events may be protocol-defined outcomes (serious fall injury). Minor adverse events are defined as conditions that may be

unpleasant and bothersome to the participant, such as sore muscles, but that do not require discontinuing the study intervention or components of the intervention. Examples of minor adverse events include but are not limited to the following: anxiety, fatigue, decreased appetite, insomnia, dizziness, muscle or joint stiffness, muscle strain or soreness, ankle or knee pain, foot pain, and other minor symptoms that may have restricted the participant's usual activities for at least ½ day like a head cold, flu or allergy problems. Minor adverse events should be reported on an annual basis to each site's own IRB.

Potential adverse events for study related activities and interventions are explained to each participant by trained study personnel during the informed consent process. Each participant is instructed to report the occurrence of an adverse event at scheduled data collection times (scheduled clinical exams or phone interviews). Participants also have access to study clinic personnel at other times to report serious adverse events or concerns about the safety of participating in the LIFE Study.

Expected serious adverse events related to the exercise intervention include in rare instances, heart attack, stroke, and death. Cardiovascular events are assessed using standard protocol measures including ECGs. When a cardiovascular event has occurred, a study physician decides whether it is permissible for the participant to continue interventions. If the LIFE interventions are discontinued for safety reasons, they may be resumed after consultation with the participant's primary care physician.

Serious fall injuries and fractures are assessed using standard protocol measures, including radiographs and hospital records. When a serious fall injury or fracture occurs, a study physician decides whether it is permissible for the participant to continue interventions. If the LIFE interventions are discontinued for safety reasons, they may be resumed after consultation with the participant's primary care physician.

In the LIFE safety monitoring system, participants who report adverse events to any staff person at any time are referred to unmasked medical staff responsible for identifying, recording, and managing these events. Safety-related events are reported in a timely fashion as required by the Data and Safety Monitoring Board and the IRBs responsible for the study. Interventionists and other staff reporting or managing adverse events for safety purposes do not at any time communicate information regarding these events to study assessment personnel.

LIFE maintains an event outcome database that is completely separate and distinct from the safety monitoring system for the intervention group. This is necessary because many of the LIFE staff members are not masked to intervention assignment, and it is critical that the identification and reporting of serious adverse events for safety reasons not bias the study's collection of outcome data. Thus, for outcome purposes, all LIFE participants are systematically queried at clinic visits or on clinic phone calls scheduled according to the protocol to capture outcome data on study outcomes, medical events, or adverse experiences. This separate outcome database contains solely those adverse events that are reported through these regularly scheduled event interviews conducted by designated outcome assessment staff who are masked to intervention assignment.

All deaths shall be reported within 48 hours to both DSMB and NIA. All Serious Adverse Events shall be reported in a summary format by the blinded treatment arm (A and B) to the DSMB and NIA monthly.

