### 7.2.1 Contact Mode and Frequency

The physical activity intervention consists of a general weekly walking goal of 150 minutes. This is consistent with the public health message from the 2008 Physical Activity Guidelines for Americans report that moderate physical activity should be performed for 30 minutes on most if not all days of the week (150-210 total minutes). This goal is **approached in a progressive manner** across the first 3 months of the trial. There are multiple ways that the goal can be achieved, based on the physical abilities and constraints of each participant. In light of the heterogeneity of the target population (with respect to physical capabilities and health status), this study will specifically define the variability in participants' ability to reach this weekly target, to estimate the dose-response relationship between incremental increases in weekly physical activity and changes in the primary and secondary outcomes, and to better specify the level of ongoing behavioral instruction needed to achieve such changes.

| Table 7.2.1. Intervention staff contacts for physical activity group |                                |                                                                                          |
|-----------------------------------------------------------------------------|--------------------------------|------------------------------------------------------------------------------------------|
| Week                                                                        | Center-Based Physical Activity | Home-Based Physical Activity                                                             |
| Adoption: weeks 1-52                                                        | 2 times each week              | 1 time/week (weeks 1-4)
2 times/week (weeks 4-8)
Up to 3-4 times/week (weeks 8-52) |
| Maintenance: weeks 53 – end                                                 | 2 times each week              | Up to 3-4 times/week                                                                     |

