#### 7.2.4. Adoption phase (weeks 1-52)

Two **center-based** exercise instruction sessions per week will be conducted in a supervised setting. These sessions will be used to initiate the walking program and to introduce participants to the strength, stretching, and balance portions of the program in a safe and effective manner. The supervised setting will allow instructors to better tailor the program to individual needs and abilities early on, so as to prevent early dropout and to facilitate the building of self-efficacy and support, which have been found to be key to long-term physical activity maintenance. These exercise sessions will involve 40-60 mins of exercise instruction. For those participants who miss 2 consecutive exercise class sessions, without informing the exercise staff of their absence, exercise staff will call the participant to problem-solve ways to get the participant back to class.

In addition, the center-based sessions will be supplemented, in a progressive fashion, by **home-based** exercises as a means of promoting physical activity in multiple settings to aid behavioral generalization and long-term adherence. This has been found to be a key feature of sustained physical activity participation among older as well as younger adults. Appropriate community based exercise facilities (e.g., YMCAs; senior centers) will be identified for those persons preferring to undertake center-based activities on a more frequent basis throughout the week.

**7.2.5. Maintenance phase (week 53 through the end of the trial):** The Maintenance phase will consist of:

- Continued twice-per-week **center-based** group exercise sessions offered to each participant.
- Progression of home-based physical activity to 3-4 times per week.
- Quarterly project **newsletters**, used to promote ongoing support and participation and to provide ongoing information related to physical exercise participation and adherence.

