### 7.3. Successful Aging Program Intervention

#### 7.3.1. Contact Mode and Frequency

The successful aging program arm meets in small groups (approximately 25 participants per group), one time each week for the first 26 weeks of the intervention. From week 27 on, successful aging groups will be offered two times per month with required participation at least once per month. Telephone calls are made after missed visits to problem-solve barriers to attendance and to encourage regular participation. As undertaken in LIFE-P, those participants randomized into the Successful Aging Program will receive an individual 45 minute face to face introductory session, by a health educator, during which time the program is described and questions are answered.

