**Table 7.2.2. Intervention staff contacts for the successful aging health education group**

| Week                      | Center-Based Workshop                                                          | Telephone Contact                                                                                       |
|---------------------------|--------------------------------------------------------------------------------|---------------------------------------------------------------------------------------------------------|
| Adoption Week 1-26        | 1 time each week                                                               | Intervention staff contact made after one missed session to problem-solve around barriers to attendance |
| Maintenance Week 27 – end | Offered 2 times per month with ongoing participation required at least monthly | Intervention staff contact if participant misses first session of the month                             |

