#### 8.4.2. Safety Measures During Physical Activity

Center based interventions are conducted at a central location and all sessions are conducted and supervised by **trained interventionists**, who monitor potential adverse experiences and symptoms. During the physical activity sessions a defibrillator and on-site trained staff are available to deal with medical emergencies. Also, institutional and community EMS services are activated if needed. As indicated previously, participants are taught the importance and proper method of **warming-up** prior to and **cooling-down** following structured activity sessions. If at any point during a physical activity session, participants develop chest pain, shortness of breath, or dizziness, they are instructed to rest and to contact the center and their physicians if these symptoms persist or recur with further physical activity. The implementation of the physical activity sessions is consistent with the recommendations published by Fletcher et al. for older adults who may have

stable cardiovascular disease.

Blood pressure and heart rate are monitored before and after the walking activity at each center-based intervention session. Blood pressure and heart rate are measured during the walking at each center based session in participants who had experienced any of the following at a previous physical activity session:

- Resting blood pressure systolic  $\geq 200$  mm Hg or diastolic  $\geq 100$  mm Hg
- Decrease in systolic blood pressure  $\geq 20$  mm Hg following the activity
- Increase in systolic blood pressure to  $\geq 250$  mm Hg or in diastolic blood pressure  $\geq 115$  mm Hg following the activity
- Resting heart rate  $\geq 120$  beats/min or  $\leq 45$  beats/min
- Increase in heart rate  $\geq 90\%$  of age predicted maximum
- Unusual or severe shortness of breath
- Chest pain or discomfort, or heartburn
- Palpitations
- Light headedness, dizziness or feeling about to faint
- A physical activity session had to be discontinued because of other symptoms, excluding musculoskeletal symptoms (e.g., knees, ankles, hips), reported by the participant.

If any of the above occurs, the individuals are instructed to seek their physician's permission before continuing with the physical activity program.

Very few persons are expected to drop out for this reason based on previous experience and cardiac-based exclusion criteria.

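### The monthly by-arm summary of serious adverse events for the DSMB does not separate events by route of report, so more frequent staff contact in the physical activity arm can appear as an excess

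*Protocol*

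**What the plan says.** Section 8.5 of the protocol describes two event streams.

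- **Safety system.** Here "participants who report adverse events to any staff person at any time are referred to unmasked medical staff", who identify, record and manage the events.
- **Outcome database.** It is kept apart so that safety reporting by people who know the assignment does not bias outcome data. "This separate outcome database contains solely those adverse events that are reported through these regularly scheduled event interviews", and masked assessors conduct those interviews on the same schedule in both arms.

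The closing paragraph of 8.5 sets the reporting rule: "All Serious Adverse Events shall be reported in a summary format by the blinded treatment arm (A and B", monthly, to the DSMB and NIA. It names neither stream as the source and asks for no breakdown by how an event became known.

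The arms meet staff at different rates. Table 7.2.1 gives PA center sessions "2 times each week" in both phases, and 7.2.5 confirms this for maintenance: "Continued twice-per-week center-based group exercise sessions offered to each participant". Interventionists run these sessions, "who monitor potential adverse experiences and symptoms" (8.4.2). SA groups meet "one time each week for the first 26 weeks of the intervention" (7.3.1); from week 27 they are "Offered 2 times per month with ongoing participation required at least monthly" (Table 7.2.2).

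**The concern.** The protocol recognizes that event identification by unmasked staff can bias a comparison, and it protects the outcome data against this. It states no matching protection for the by-arm safety summary. If the same event has more chances to be mentioned, or is mentioned sooner, in one arm, a table of all serious adverse events (SAEs) will lean toward that arm even when true rates are equal. Labelling the arms A and B does not correct this, because the imbalance arises before the table is made.

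At stake is how the DSMB reads an imbalance. Section 8.1 lets it recommend discontinuation for an adverse effect of the intervention, and 9.2 leaves adverse events to its judgment. A modest excess in PA would be hard to interpret from the all-source table alone.

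**Working it through.** The protocol states no contact ratio, so there is no figure to reproduce. The ratios below follow from its schedules.

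**Inputs**
- PA: 2 center sessions a week throughout (Table 7.2.1; 7.2.5).
- SA: 1 a week for 26 weeks, then 2 a month offered and 1 a month required (7.3.1; Table 7.2.2).
- Follow-up: mean 2.7 years = 32.4 months, range 23 to 42 months (3.1).
- Weeks per month: 365.25 / 12 / 7 = 4.348.

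**Ratio by period (PA:SA)**
- Weeks 1-26: 2 / 1 = 2.0.
- From week 27, SA sessions offered: 2 × 4.348 / 2 = 4.3.
- From week 27, SA sessions required: 2 × 4.348 / 1 = 8.7.

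**Cumulative ratio at 2.7 years**
- Weeks: 32.4 × 4.348 = 140.9. PA contacts: 2 × 140.9 = 282.
- SA months after week 26: (140.9 − 26) / 4.348 = 26.4.
- SA offered: 26 + 2 × 26.4 = 79, ratio 3.6. SA required: 26 + 26.4 = 52, ratio 5.4.
- The same calculation at 23 and 42 months gives 3.3 to 5.9 across both SA bases.
- Adding five 6-monthly assessment visits to each arm at 2.7 years gives 3.4 to 5.0.

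These are scheduled contacts, not attendance. They omit missed-session calls, which follow one missed session in the SA adoption phase (Table 7.2.2) but two consecutive unannounced misses in PA (7.2.4). Those calls narrow the gap by an amount the protocol does not allow one to compute.

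**Timing.** The interval between scheduled contacts is about 3.5 days in PA. In SA it is 7 days at first, then 15 (offered) or 30 (required). The masked interviews are about 183 days apart in both arms.

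**Which events are exposed**

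| Event type | Ascertainment described | Likely distortion |
|---|---|---|
| Death | Tracked in both arms (10.6); reported within 48 hours (8.5) | Little |
| Hospitalization | Asked about in both arms at each clinic visit or telephone contact (10.6) | Mainly earlier reporting in PA |
| Other SAEs, such as test results and important medical events (8.5) | Blood pressure and heart rate taken at every PA center session (8.4.2); no SA counterpart described | Possible lasting detection gap |

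**Illustration, all inputs assumed.** Suppose true SAE rates are equal, a share s of SAEs is known only if volunteered, and the rest are fully captured in both arms. The apparent PA:SA ratio is [(1 − s) + s·c_PA] / [(1 − s) + s·c_SA], where c is the capture rate.
- s = 0.10, c_PA = 0.9, c_SA = 0.7: 0.99 / 0.97 = 1.02.
- s = 0.50, c_PA = 0.8, c_SA = 0.4: 0.90 / 0.70 = 1.29.

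The protocol supports no particular value of s or c. The example shows only that ratios of this order can arise without harm, and that they lie far below the contact ratio.

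**The case against.** The strongest reply is that the safety reporting is inclusive and prompt by intention, and that the means to check an imbalance already exist. Four parts of it stand.

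- **The source is not stated.** That the summary draws on the safety system is the natural reading of a rule covering all SAEs every month, next to a statement in 8.5 that safety-related events are reported as the DSMB requires. It remains an inference.
- **The gravest events are sought in both arms.** For deaths and hospitalizations there is little lasting detection gap, and cumulative counts catch up at the scheduled visits.
- **The DSMB can ask.** Section 8.1 lets it set the format of its reports, request further safety data and propose analyses.
- **Prompt reporting has value.** Replacing the monthly comparison with a table up to six months behind could delay recognition of real harm.

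A reader might go further and infer that a true PA excess could never be told apart from detection, or that the trial cannot weigh benefit against risk. The documents do not support this: the masked database questions all participants on medical events and adverse experiences, and it allows the separation. Nor does the protocol say that the DSMB decides from this one table; 9.2 refers to adverse event data and other safety issues together. The absence of a formal adverse event boundary in 9.2 adds little, because a boundary limits error from repeated looks and does not remove unequal ascertainment. All-cause mortality has its own boundary in Appendix B.

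What the reply leaves open is that 8.5 neither identifies the equal-schedule source as the comparable one for the DSMB nor calls for the route of report to be kept. A route not recorded when the event is reported may not be recoverable when an imbalance appears.

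**Conclusion.** The point holds as a limited and inexpensive improvement. As written, the monthly A/B summary is open to differential detection and earlier reporting in PA. The imbalance in opportunity follows from the stated schedules: 2 to 1 in weeks 1-26, about 4.3 to 8.7 to 1 afterwards, and about 3.6 to 5.4 to 1 over 2.7 years, before missed-session calls. The upper end of each range sets PA sessions offered against the SA required minimum; offered against offered gives 4.3 and 3.6.

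A contact ratio must not be read as an event ratio. The effect on SAE counts is unknown, is expected to be far smaller, and should fall mainly on SAEs without hospitalization and on the timing of hospitalization reports. The conclusion rests on the reading that the all-SAE summary includes events volunteered at intervention contacts. If the masked database alone was meant, 8.5 should say so.

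**What to change.** In section 8.5:

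1. Keep the monthly all-SAE summary and the 48-hour death reporting unchanged.
2. Record the route of report for each SAE: intervention contact, self-report or scheduled interview.
3. Add to the DSMB report a parallel by-arm table built only from the masked scheduled-interview database, and identify it as the comparison with equal ascertainment.
4. Note beside the all-source table that it is subject to unequal contact between arms.

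The cost is one paragraph in the protocol, one field on the event form and one more table. The parallel table will lag events by up to about six months, which is why the monthly summary must stay.

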## **8.6. Confidentiality**

The information below relates to all collaborating performance sites for the study. Data are used only in aggregate and no identifying characteristics of individuals are published or presented. Results of testing are sent to participant's private physicians if

participants agree to this. Alert values for all medically relevant procedures (e.g., ECGs) are developed, and a system is in place to alert study physicians and participants' private physicians, depending on the urgency of the values.

Confidentiality of data is maintained by using research identification numbers that uniquely identify each individual. Safeguards are established to ensure the security and privacy of participants' study records. The information collected from participants in this study has a low potential for abuse, since the data do not address sensitive issues. Nevertheless, appropriate measures are taken to prevent unauthorized use of study information. The research ID number is used. The research records are kept in a locked room in the Field Center. The files matching participants' names and demographic information with research ID numbers are kept in a separate room and are stored in a locked file that uses a different key from that of all other files. Only study personnel have access to these files. After the study is completed, local data are stored with other completed research studies in a secured storage vault.

In compliance with the Health Insurance Portability and Accountability Act (**HIPAA**) and the Standards for Privacy of Individually Identifiable Health Information of the Department of Health and Human Services, LIFE accesses personal health information and **medical records** only after receiving signed **informed consent**. Participants' medical records are obtained, reviewed and abstracted. Such records are in a locked cabinet that is separate from other files cabinets and that uses a different key from that of all other files.

**Biological samples.** LIFE complies with the OHRP requirements and guidelines related to the research use of stored biological samples as stated in "Issues to consider in the research use of stored data or tissues" from the OPRR.

(<http://ohrp.osophs.dhhs.gov/humansubjects/guidance/reposit.htm>).

**Use of stored biological samples by other investigators.** Biological samples may be used by investigators other than the investigators of the current study. The use is limited to non-commercial purposes.

**Storage and disposal of data and biological material.** Data, DNA and other biological components are stored for up to 40 years after study completion after which time all data and samples will be destroyed. All specimens have numerical samples IDs with no personal identifiers.

